### Intervention

Participants will be randomized to receive either placebo (maltodextrin 3.3 g orally/day; Agenamalt 20.222, Agrana Starch, Konstanz, Germany) or prebiotic (oligofructose-enriched inulin 8 g orally/day; Synergy1, Beneo, Mannheim, Germany). Inulin and oligofructose are approved as food ingredients in Canada and have been used previously in clinical trials [8, 25]. Both the prebiotic and placebo will be provided to participants in powder form in identical foil pre-weighed packets. Participants will be instructed to mix the packet with 250 mL of water until dissolved and to drink it 15–20 minutes prior to their evening meal. For the first 2 weeks, participants will be asked to only take half of the dose in order to minimize gastrointestinal side effects, and then they will take the full dose for the remaining 10 weeks.

Participants will be asked to record any diabetes-related or gastrointestinal adverse reactions, i.e. frequency of mild hypoglycemia (symptoms of hypoglycemia with a blood glucose less than 4 mmol/L and able to self-treat with oral rapid-acting carbohydrate), severe hypoglycemia (symptoms of hypoglycemia with a blood glucose less than 4 mmol/L but requires assistance with treatment due to decreased level of consciousness or has a seizure), diabetic ketoacidosis or flatulence. At the end of the 12 weeks, participants will be asked to return any remaining packets of placebo or prebiotic in order to assess for compliance. Telephone contact from a member of the research team will occur monthly to encourage compliance and recording of adverse reactions.

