The primary objective of this study is to determine the effect of a 12-week dietary intervention with 8 g/day of prebiotic intake compared to placebo on glycemic control as measured by HbA1c in children diagnosed with DM1 for at least one year. The secondary objective is to determine the gut microbiota composition in children diagnosed with DM1 consuming prebiotic versus placebo. Further, we aim to examine the differences in gut permeability, serum inflammatory markers, glucagon-like peptide 1 (GLP-1) and GLP-2 and C-peptide in children diagnosed with DM1 consuming prebiotics versus placebo and to assess for diabetes-related adverse reactions (i.e. severe hypoglycemia and diabetic ketoacidosis) associated with use of prebiotics in children with DM1.

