### Analysis

Analysis will be performed using SPSS 22.0 software (IBM, New York, USA). Results will be considered statistically significant if *p* ≤ 0.05. Baseline descriptive data between the control and intervention group will be compared using chi-square for categorical variables and *t* tests for continuous variables. The primary outcome of HbA1c will be expressed as mean HbA1c values with standard deviations, and a two-sided *t* test will be used to compare HbA1c between placebo and prebiotic groups. Differences between the placebo and prebiotic groups’ C-peptide, inflammatory markers (IL-6, IFN-gamma, TNF-alpha, and IL-10), GLP-1, GLP-2 and intestinal permeability will be compared using a two-sided *t* test. Adverse events will be presented as the proportion of each event seen in each group (placebo and prebiotic). An intent-to-treat analysis will be used with the last data point carried forward for missing data. A secondary analysis will also be performed on a per-protocol basis with all subjects who have completed the intervention and are reported to be compliant with ≥80 % of the prebiotic or placebo packets consumed.

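### The instruction to record any gastrointestinal reaction is then defined by a list with flatulence as its only gut item, so gut tolerability may be recorded incompletely or unevenly

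*Protocol article*

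**What the plan says.** In the protocol article, Methods/design, Intervention, the recording instruction reads "Participants will be asked to record any diabetes-related or gastrointestinal adverse reactions, i.e. frequency of mild hypoglycemia". It goes on to severe hypoglycemia and closes with "diabetic ketoacidosis or flatulence". That makes four items: mild hypoglycemia, severe hypoglycemia, ketoacidosis and flatulence.

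The same section explains that for the first two weeks participants "only take half of the dose in order to minimize gastrointestinal side effects". No particular side effect is named there.

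Other places that bear on the point:

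- Intervention, prompting: "Telephone contact from a member of the research team will occur monthly to encourage compliance and recording of adverse reactions".
- Background, objectives paragraph: the safety aim is "to assess for diabetes-related adverse reactions (i.e. severe hypoglycemia and diabetic ketoacidosis) associated with use of prebiotics".
- Data collection: the safety items named for the visits are ketoacidosis, severe hypoglycemia and mild hypoglycemia. The section refers to Table 2 for the data collected; Table 2 is not shown in the text available.
- Gut microbial profiling: Bristol stool type is marked alongside the stool samples at baseline, 3 and 6 months.
- Analysis: "Adverse events will be presented as the proportion of each event seen in each group".

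**The concern.** The sentence gives two different scopes. Its opening covers every gastrointestinal reaction; its definition covers one. A person designing the participant record, or a parent filling it in, has to choose between them, and different people may choose differently.

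What is at stake is the gut tolerability information from a pilot whose stated purpose is to test feasibility for a larger trial. The plan expects gut effects broad enough to shape the start of dosing. If only flatulence is asked for, symptoms such as abdominal pain, bloating, nausea, vomiting or diarrhea enter the record only when a family volunteers them. The proportions by arm then depend on who volunteers as well as on what happened. Symptoms not written down at the time are hard to recover afterwards.

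**Working it through.** No figure in the plan is in dispute here, so the check is mainly a comparison of the text with itself.

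**1. Is the list open or closed?** The definition is introduced by *i.e.*, which means 'that is', and it ends on *or* with no 'etc.' or 'other'. The article marks open lists when it wants them: Table 1 gives 'examples' followed by 'etc.', and the Randomization and Gut microbial profiling sections use *e.g.* The objectives paragraph uses *i.e.* in the defining sense, to limit the diabetes-related reactions to two named events. By the article's own usage, the closed reading is the natural one.

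**2. Does the closed reading fit the rest of the section?**

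| Place in Intervention | Scope of gut effects |
|---|---|
| Opening of the recording instruction | any gastrointestinal reaction |
| Definition after *i.e.* | flatulence only |
| Reason for the half-dose start | gastrointestinal side effects, plural and general |

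The second row agrees with neither of the others.

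**3. Does another stated element close the gap?**

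- The monthly calls encourage recording of adverse reactions but name no symptoms, so they lead back to the same definition.
- The visit items named in the text are all diabetes-related.
- The Bristol chart describes stool form around three sampling times. It does not record pain, bloating, nausea or vomiting, and is not described as an adverse-event record.
- The Analysis section reports each event by arm, so what it can report depends on what was recorded.

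**4. What incomplete recording does to the comparison.** Suppose a symptom truly occurs in proportions p1 (prebiotic) and p0 (placebo), and that an affected child's symptom reaches the record with probability r, the same in both blinded arms. The equal r is an assumption. Then

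expected recorded difference = r × p1 − r × p0 = r × (p1 − p0).

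With r = 1 the record is complete. With r = 0, a list enforced as closed, the recorded difference is zero whatever the truth. In between, any true difference shrinks towards zero. Blinding helps to keep r equal between arms; it does not bring r to 1. A recorded count of zero could mean that nobody had the symptom or that nobody was asked.

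**5. Scale.** The Internal pilot section enrolls 15 per arm. One affected child left unrecorded changes that arm's proportion by 1/15 = 6.7 percentage points. Among the 12 expected completers per arm it is 1/12 = 8.3 points. The plan also assumes 20 % drop-out, 0.20 × 15 = 3 children per arm. If one of them stopped because of, say, abdominal pain, none of the four listed events would show it.

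**The case against.** The strongest reply is that the governing words are broad. A child with vomiting or abdominal pain plainly has a gastrointestinal reaction, and if the list were closed, the word 'any' would do no work. *I.e.* may have been written where *e.g.* was meant. The calls encourage recording without limiting its type, and the Analysis section does not restrict itself to the four events. Table 2 and the participant record cannot be seen.

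Much of this stands, and it rules out several stronger readings that a reader might infer:

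- **That the other gut symptoms are not captured.** This is not established. 'Any' may prevail in practice, and the forms are not shown.
- **That reactions neither gut- nor diabetes-related have no route into the record.** General adverse-event procedures, with dates and grading, are commonly left to the full protocol. Their absence from an article shows nothing.
- **That the product will be called low-risk on the strength of this record.** The article uses that description as a premise, qualified by 'potentially', in the Abstract and Background. It plans no such conclusion from these data.
- **That the full trial's dose will be chosen from this record.** No section says so.
- **That a given number of children would be missed.** The documents give no symptom rate from which to calculate one.

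The reply does not remove the inconsistency. If *i.e.* was a slip, the sentence still needs correcting, because those using it cannot know that. An instruction that asks for everything but names one gut symptom also invites uneven reporting.

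**Conclusion.** The point holds as an internal inconsistency with a practical consequence. The recording instruction asks for any gastrointestinal reaction, defines the reactions with flatulence as the only gut item, and sits beside a half-dose start aimed at gut side effects in general. Followed literally, it yields a gut tolerability record of flatulence alone; followed loosely, one that varies from family to family. Either way the by-arm proportions would be incomplete for a feasibility pilot.

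The loss cannot be quantified from the documents beyond the 6.7 percentage points per unrecorded child in an arm of 15. The conclusion rests on the published wording and would fall away if the participant record in use already asks for the other gut symptoms. No stated sample size or power figure is affected. The change is worth making but does not threaten the trial's validity.

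**What to change.** In the Intervention section, replace *i.e.* with 'including', and name abdominal pain, bloating, nausea, vomiting and diarrhea next to flatulence, both in the text and on the existing participant record. In the Analysis section, state that these symptoms will be reported as proportions by arm with the other events. If the record already lists them, correcting the sentence is enough.

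The cost is a few lines on a form already in use and wording changes in two sections. A longer prompt list will bring in more minor reports, in both blinded arms. The Trial status section says recruitment has just commenced, so the change should be made early, with a note of which children, if any, began on the former record. No dose or treatment rule is touched.

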### Data collection

Study visits will be coordinated with diabetes clinic visits; the data to be collected are outlined in Table 2. Demographic information will be collected at baseline. Anthropometric measures and assessment of insulin regimens, frequency of diabetic ketoacidosis (DKA) in previous 3 months, frequency of severe hypoglycemia in previous 3 months and average number of mild hypoglycemic episodes per week in the preceding 3 months will be assessed at baseline, 3 months and 6 months.

**Table 2 Tab2:**
[figure not shown]
Study procedures and data collection

#### Glycemic control, inflammatory markers, GLP-1 and GLP-2

Blood will be collected at baseline, 3 months and 6 months for serum C-peptide, HbA1c, serum inflammatory markers (IL-6, IFN-gamma, TNF-alpha and IL-10), GLP-1 and GLP-2. Serum will be sent to Calgary Laboratory Services (Calgary, AB, Canada) for measurement of HbA1c by turbidimetric inhibition immunoassay (Roche Integra 800 CTS, Basel, Switzerland) and serum C-peptide by chemiluminescent assay (Siemens Immulite 2000, Erlangen, Germany). Serum inflammatory markers will be analysed by Milliplex Human Cytokine Magnetic Bead Multiplex kits (Millipore, St. Charles, MO, USA). GLP-1 and GLP-2 will be measured with ELISA kits (Millipore, St. Charles, MO, USA).

#### Intestinal permeability

Intestinal permeability will be assessed at baseline, 3 months and 6 months. Participants will consume a regular evening meal and then 3 hours later, prior to bedtime, drink a solution containing lactulose (5 g), mannitol (2 g) and 3-O-methylglucose (5 g) in 200 mL of water (Biosource, Canada). All urine for the following 12 hours will be collected with 5 mL thymol in the storage container for preservation, and stored frozen. High-performance liquid chromatography (HPLC) will be used to analyse urine samples for the lactulose, mannitol and 3-O-methylglucose content. Urine samples will be filtered through a 0.4-μm filter and diluted as necessary. Samples will be deionized and injected into an ion exchange column and eluted with NaOH at a flow rate of 0.4 mL/min with concentrations ranging from 400 to 600 mM. Peaks will be detected using pulse and amperometric detection in a Dionex HPLC. The fraction of the ingested dose recovered in the urine sample will be calculated and compared between the two groups [26, 27].

#### Gut microbial profiling

Stool samples will be collected at baseline, 3 months and 6 months as previously described [14, 20]. Participants will be provided with a Bristol stool chart and asked to mark down the type of stool (type 1 to type 7). Participants will be provided a stool collection kit and will be instructed on proper methods for stool collection. One tablespoon of stool will be placed in a pre-labelled sterile conical tube, placed in a biohazard bag and stored in the home freezer (–20 °C). Participants will bring samples to the laboratory up to 3 days from collection on ice, and then the samples will be stored in the laboratory freezer at –80 °C until analysed. Total bacterial DNA will be extracted from stool samples using the FastDNA Spin Kit for Feces (MP Biomedicals, Lachine, QC, Canada) followed by ethanol precipitation purification. DNA will be quantified using Qubit dsDNA assay (Promega, Madison, WI, USA) and diluted to 5 ng/μL concentration. Microbial composition will be determined as per our previously published protocol [28] following Illumina’s 16S rRNA amplicon sequencing protocol on the MiSeq platform (Illumina, San Diego, CA, USA). The V3 and V4 regions of the 16S rRNA gene will be amplified using 2.5 μL (5 ng/μL) microbial DNA, 5 μL (1 μM) of gene-specific primers and 12.5 μL 2x KAPA HiFi Hotstart Ready Mix (KAPA Biosystems, Boston, MA, USA). Following amplification, the PCR product will be purified (Ampure XP beads, Beckman Coulter, Mississauga, ON, Canada) and the amplicon size confirmed. Dual-indexed barcodes will be attached to amplicon targets in a second PCR stage. The final PCR product will be purified (Ampure XP beads, Beckman Coulter, Mississauga, ON, Canada) and quantified using the Qubit dsDNA assay (Promega). Amplicon size will be assessed using a D1000 TapeStation (Agilent Technologies) assay and samples normalized to 4 nM using 10 mM Tris pH 8.5. After pooling barcoded libraries, samples will be denatured and diluted to a final concentration of 4 pM, and a final product containing 10 % PhiX will undergo dual-indexed paired 300 bp sequencing on the MiSeq using Reagent kit v3 (Illumina). Paired-end reads will be merged using PEAR (Paired-End read merger) [29], and data analysis will be performed using the Quantitative Insights into Microbial Ecology (QIIME) pipeline version 1.9.1 [30]. Operational taxonomic units (OTUs) will be picked using UCLUST [31] with a 97 % sequence identity threshold followed by taxonomy assignment using the latest Greengenes database (http://greengenes.secondgenome.com). To evaluate beta diversity, principal coordinate analysis (PCoA) on weighted UniFrac distances will be performed on all OTUs using QIIME. Alpha diversity will be measured by calculating the Shannon index, Simpson index and Chao1 metrics using QIIME [30]. A false discovery rate will be used to control for type 1 error. Given that 16S rRNA sequencing generates relative abundance data, we will also quantify the abundance of select microbial groups (e.g. *F. prausnitzii*, *Bifidobacterium* spp., total bacteria) with quantitative PCR according to our previous work [14, 20] using the Bio-Rad iCycler (Bio-Rad Inc., Mississauga, ON) and group-specific primers.

### Sample size

#### Internal pilot

The initial pilot study will aim to test the feasibility of a fully powered studied in children with type 1 diabetes. To test feasibility in this pilot study, we will enroll 15 subjects per arm. If we assume a drop-out rate of 20 % (12 subjects completing the study in each arm), power of 80 %, and alpha of 0.05 and a standard deviation of 1.3 for HbA1c, then with the pilot study we would be able to detect a mean difference in the absolute HbA1c of 1.5 between the placebo and prebiotic groups.

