## Abstract

**Background:**

The gut microbiome is increasingly recognized as a contributor to disease states. Patients with type 1 diabetes (DM1) have distinct gut microbiota in comparison to non-diabetic individuals, and it has been linked to changes in intestinal permeability, inflammation and insulin resistance. Prebiotics are non-digestible carbohydrates that alter gut microbiota and could potentially improve glycemic control in children with DM1. This pilot study aims to determine the feasibility of a 12-week dietary intervention with prebiotics in children with DM1.

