**Discussion:**

This is a novel pilot study designed to test feasibility for a fully powered study. We hypothesize that consumption of prebiotics will alter gut microbiota and intestinal permeability, leading to improved glycemic control. Prebiotics are a potentially novel, inexpensive, low-risk treatment addition for DM1 that may improve glycemic control by changes in gut microbiota, gut permeability and inflammation.

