#### Full trial

For the full study, the sample size was calculated for a two-sided *t* test comparing two independent samples. Based on previous follow-up data from the Alberta Children’s Hospital Diabetes Clinic, the mean score of HbA1C at baseline in both groups will be estimated to be 8.4 with a standard deviation of 1.3 for each group. A clinically significant change in absolute HbA1c of 0.5 will be used, as this threshold has been used in previous drug trials to demonstrate effectiveness in diabetes. For a power of 80 % and an alpha of 0.05, the number of subjects needed per arm of the study is 107. If we assume a drop-out rate of 20 %, then approximately 135 subjects per arm of the study will be required in a fully powered study.

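### The pilot is justified and sized on feasibility, but its primary objective and primary analysis are an HbA1c efficacy test with about 15% to 17% power for the plan's own clinically significant difference

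*Protocol article*

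**What the plan says.** Three places in the protocol article describe a feasibility study.

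- Abstract, Background: "This pilot study aims to determine the feasibility of a 12-week dietary intervention with prebiotics in children with DM1".
- Abstract, Discussion: "This is a novel pilot study designed to test feasibility for a fully powered study".
- Sample size, Internal pilot: "To test feasibility in this pilot study, we will enroll 15 subjects per arm".

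Two places describe an efficacy study.

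- The objectives at the end of the Background section: "The primary objective of this study is to determine the effect of a 12-week dietary intervention with 8 g/day of prebiotic intake compared to placebo", with glycemic control measured by HbA1c. The secondary and further objectives cover microbiota, gut permeability, inflammatory markers, GLP-1, GLP-2, C-peptide and diabetes-related adverse reactions.
- The Analysis section names HbA1c as the primary outcome, compares the groups by a two-sided t test, and declares significance at p ≤ 0.05.

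The Internal pilot section supports 15 per arm with a detectable difference of 1.5 HbA1c points, assuming "12 subjects completing the study in each arm", 80% power, "and alpha of 0.05 and a standard deviation of 1.3 for HbA1c". The Full trial section then sets the difference of interest: "A clinically significant change in absolute HbA1c of 0.5 will be used". It states that 107 per arm are needed for that difference, or about 135 after 20% dropout.

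**The concern.** Feasibility and HbA1c efficacy cannot both be the pilot's primary question, and the plan serves neither well. Feasibility is the declared aim, yet it does not appear among the listed objectives or analyses. Returned packets are counted (Intervention section), but the Analysis section uses compliance only to define the per-protocol set. Adverse events are tabulated as safety data. HbA1c efficacy is the declared primary objective, yet the sample was not chosen to answer it at the difference the plan considers important.

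If the plan is followed as written, the headline result is a significance verdict on HbA1c that 30 children cannot support. Whether a full trial is feasible would have no planned analysis. A non-significant primary outcome could be read as evidence against the prebiotic, and a significant one would come with an inflated estimate.

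**Working it through.** **Inputs, all from the article.** SD 1.3; two-sided α = 0.05; 1:1 allocation; 15 enrolled and 12 completing per arm; clinically significant difference 0.5. Both n = 12 and n = 15 are used, because the intent-to-treat rule with the last value carried forward could keep all 15 in the analysis.

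**Step 1: reproduce the plan's figures.**

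- Pilot detectable difference by normal approximation: SD × √(2/n) × (z₀.₉₇₅ + z₀.₈₀) = 1.3 × √(2/12) × (1.960 + 0.842) = 0.531 × 2.802 = 1.49. This matches the stated 1.5. The exact t calculation gives 1.56, with power of 77.1% at 1.5.
- Full trial: n = 2 × (1.3 × 2.802 / 0.5)² = 106.1, rounded up to 107 per arm, as stated. Then 107 / 0.8 = 133.75, so 134, against the stated figure of about 135.

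The plan's arithmetic is therefore sound.

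**Step 2: power of the primary test for 0.5.** Noncentral t with 2n − 2 degrees of freedom and noncentrality 0.5 / (1.3 × √(2/n)).

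| Per arm | Standard error | Noncentrality | Power, exact t | Power, normal |
|---|---|---|---|---|
| 12 | 0.531 | 0.942 | 14.7% | 15.4% |
| 15 | 0.475 | 1.053 | 17.4% | 18.2% |

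On the exact figures, the chance of a non-significant result when 0.5 is real is 85.3% (12 per arm) or 82.6% (15 per arm).

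**Step 3: expected precision.** The 95% CI half-width is t₀.₉₇₅,₂ₙ₋₂ × 1.3 × √(2/n).

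- 12 per arm: 2.074 × 0.531 = 1.10.
- 15 per arm: 2.048 × 0.475 = 0.97.

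Both are about twice the 0.5 of interest. An interval centred on 0.5 would run from −0.60 to 1.60, or from −0.47 to 1.47.

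**Step 4: exaggeration when the result is significant.** I simulated the stated t test 1,000,000 times with a true difference of 0.5 and SD 1.3. Among significant results, the mean absolute estimate is 2.6 times the truth at 12 per arm and 2.35 times (about 2.4) at 15 per arm.

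**Step 5: would baseline adjustment rescue it?** The article does not plan adjustment and gives no correlation between baseline and follow-up HbA1c. I assume r = 0.5 to 0.8 and replace the SD by 1.3 × √(1 − r²). Power for 0.5 is then 18% to 32% at 12 per arm and 22% to 40% at 15 per arm, still far below 80%.

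**Step 6: what 30 children can say about feasibility.** If 24 of 30 are retained (the plan's assumed 80%), the exact 95% CI is 61% to 92%. That is coarse, but it answers the stated aim directly.

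**The case against.** **The low power is disclosed.** This stands. The article states 1.5 as detectable, 0.5 as clinically significant and 107 per arm as the number needed for 0.5. A reader might infer a hidden or mistaken calculation, but the documents show neither. The fault is that aim, objective and analysis do not match.

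**An internal pilot normally shares the full trial's primary outcome.** The Sample size section does use that heading. But the objectives speak of this study, and the Background presents the pilot as groundwork for later trials. Nothing shown carries the pilot's participants or its primary test into the full trial, so the heading does not settle the conflict.

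**The pilot also aims at proof of concept.** The Background says so, and between-group comparisons serve that purpose. Estimates with intervals would serve it as well, without making an HbA1c significance test the primary analysis.

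**A journal article condenses the protocol.** This stands in part. Numeric progression criteria may sit in the full protocol, and the data-collection table and flow diagram are not visible in the text reviewed, so their absence is not held against the plan. The conflict over the primary objective is within the article itself.

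**A failed test need not stop the programme.** Also fair. No text ties the full trial to the pilot's p-value, and the full trial is sized from clinic data and the 0.5 threshold, not from the pilot's estimate. The risk is misreading, not a planned stopping rule.

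**Conclusion.** The point holds. The article justifies and sizes the pilot on feasibility but makes an HbA1c test at p ≤ 0.05 its primary objective and analysis, and none of its listed objectives or analyses addresses feasibility. With SD 1.3 and two-sided α = 0.05, power for the plan's own 0.5 is 14.7% (12 per arm) to 17.4% (15 per arm), and the expected 95% CI half-width is 1.10 to 0.97. A real 0.5 would be missed about 83% to 85% of the time.

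A reader might take the ratio 1.5 / 0.5 to mean that a significant result would be inflated threefold. That ratio compares the detectable difference with the important one. The expected inflation is about 2.4- to 2.6-fold.

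The 15-per-arm figures assume that carried-forward values behave like observed ones. Baseline values carried forward for dropouts would dilute a true difference, so 17.4% is more likely generous than strict.

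**What to change.** Reconcile the objectives and the Analysis section with the Abstract and the Internal pilot section.

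1. Make feasibility the pilot's primary objective. Report, each with an exact 95% CI: retention, set against the assumed 80%; the proportion of participants taking at least 80% of their packets; and completeness of blood, stool and urine samples. The planned visits, sample collections and packet returns already generate these data.
2. Do not treat the article's 80% compliance figure as a ready-made progression threshold. It is a per-participant cut-off for the per-protocol set and does not say what share of participants must reach it.
3. Include a consent rate only if a log of those approached is kept. Families may also come forward through posters and pamphlets, so the denominator is otherwise undefined.
4. Report HbA1c as a secondary outcome: a baseline-adjusted group difference with its 95% CI and no significance verdict. State that a non-significant result is not evidence against a 0.5 effect.

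**Cost.** Rewording and possibly a registry update, with no extra participants or procedures. The pilot gives up a confirmatory efficacy claim, which it cannot support. The Trial status section says recruitment had only just begun, so at that stage the change could be made ahead of outcome data.

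### Minor: the pilot's detectable HbA1c difference of 1.5 is a normal-approximation figure, slightly optimistic for the planned t test with 12 completers per arm (77% power at 1.5; 80% at 1.56)

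*Protocol article*

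**What the plan says.** The Internal pilot paragraph gives testing feasibility as its aim and says "we will enroll 15 subjects per arm". It then allows for 20% drop-out, which leaves 12 completers in each arm, and takes "power of 80 %, and alpha of 0.05 and a standard deviation of 1.3 for HbA1c". From these inputs it concludes "we would be able to detect a mean difference in the absolute HbA1c of 1.5" between the two arms. The paragraph names neither the formula nor whether alpha is one- or two-sided.

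The Analysis section fixes the test for the primary outcome: "a two-sided *t* test will be used to compare HbA1c between placebo and prebiotic groups". It also says that the analysis is by intent to treat, with the last data point carried forward where data are missing.

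The Full trial paragraph says that its own sample size was calculated for a two-sided t test. It gives 107 per arm for a difference of 0.5 with the same SD, power and alpha.

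**The concern.** The normal approximation treats the SD as known. The planned t test estimates it from the data, here from 24 children if only completers are counted. At more than 100 per arm this makes almost no difference; at 12 per arm it is visible. The pilot sentence does not call its figure approximate, and both the Full trial paragraph and the Analysis section refer to a two-sided t test. A reader will therefore take 1.5 as the t-test figure.

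The stake is limited to interpretation. HbA1c is the primary objective, and 1.5 is the only statement of what the pilot could detect. A null result would be read against it, so it should match the planned test.

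**Working it through.** **Inputs.** From the Internal pilot paragraph: n = 12 completers per arm (15 enrolled less 20%), SD = 1.3, alpha = 0.05, power = 80%, stated difference 1.5. From Analysis: two-sided two-sample t test. From Randomization: 1:1 allocation.

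**1. Reproducing the stated figure (normal approximation).**
- Standard error of the difference: 1.3 × √(2/12) = 0.5307.
- Detectable difference: 0.5307 × (1.960 + 0.842) = 1.487, which rounds to 1.5.
- Required n for 1.5: 2 × (2.8016)² × 1.3² / 1.5² = 11.8, so 12 per arm. Power at 1.5 with 12 per arm is 80.7%.

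The stated figure reproduces.

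**2. The planned test (two-sided t, noncentral t distribution, 22 degrees of freedom).**
- Critical value: 2.074 instead of 1.960.
- Noncentrality at 1.5: 1.5 / 0.5307 = 2.826.
- Power at 1.5: 77.1%, which is 2.9 points below 80%.
- Difference with 80% power: 1.1968 × 1.3 = 1.556, which rounds to 1.6.
- Completers needed for 1.5: 13 per arm (80.6%); 12 per arm falls short.

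**3. Does the full-trial figure suffer in the same way?** The normal approximation gives 2 × (2.8016)² × 1.3² / 0.5² = 106.1, so 107 per arm, as stated. The t test at 107 per arm has 79.97% power. The choice of formula is immaterial there.

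**4. The intent-to-treat analysis with carried-forward values.** This can include up to 15 per arm. HbA1c is measured at baseline, 3 months and 6 months, so a child who leaves before month 3 contributes a baseline value with no treatment effect. If k of 15 per arm do so, the expected difference is 1.5 × (15 − k)/15. With the SD held at 1.3 (an assumption), t-test power at 15 per arm is:

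| Children per arm carrying baseline forward | Expected difference | Power |
|---|---|---|
| 0 | 1.5 | 86.2% |
| 1 | 1.4 | about 81% |
| 2 | 1.3 | about 75% |
| 3 (the full 20%) | 1.2 | about 68% |

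With 15 per arm and no dilution, the difference detectable with 80% power is 1.378.

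**The case against.** The best defence is that 1.5 is not a miscalculation. It follows from the stated inputs by a standard formula, and the same formula returns the protocol's 107 per arm, so the document is consistent with itself. The discrepancy is one completer per arm. It also lies within the precision of the SD: an SD of 1.25, which would be printed as 1.3, gives 1.1968 × 1.25 = 1.496 by the t test. All of this stands and is why the point is minor. It does not remove the point, because with the SD as printed the t-test value rounds to 1.6, and nothing in the paragraph marks 1.5 as approximate.

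A reader might go further and infer that the planned primary analysis has only 77% power for 1.5. The documents do not support that. The 77% belongs to a comparison of 12 completers per arm, whereas the planned analysis is intent to treat with values carried forward and could include 15 per arm. Its power could lie above or below 77%, depending on when children drop out, which the article does not say. Equally, the 86% at 15 per arm does not rescue the stated figure: it needs an undiluted effect in the dropouts, and the protocol bases its sentence on the 12 completers.

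A reader might also infer that the pilot is undersized. That does not follow either, because the 15 per arm was set to test feasibility and 1.5 describes what that number can detect.

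**Conclusion.** The point holds as a minor correction. On the protocol's own basis of 12 completers per arm, SD 1.3 and alpha 0.05 (two-sided, as in Analysis), the planned t test has 77% power for 1.5 and 80% power for 1.56. The stated figure is optimistic by about 0.06 to 0.07 HbA1c units: 1.556 against 1.5 as printed, or against 1.487 before rounding. This rests on equal arms and on the SD being 1.3 as printed. The power of the intent-to-treat analysis remains a range, about 68% to 86% for zero to three carried-forward baselines per arm. Neither the pilot's enrolment nor the full-trial sample size is affected.

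**What to change.** Restate the last sentence of the Internal pilot paragraph along these lines: *with 12 completers per arm, SD 1.3 and two-sided alpha 0.05, a t test has 80% power for a difference of about 1.6 (1.56), or 77% for 1.5.* Say that the figure applies to completers and that the power of the intent-to-treat analysis with carried-forward values depends on when dropouts occur. The cost is one or two sentences and a slightly less favourable figure. No extra participants and no change of design or analysis are needed.
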